## Abstract

**Background:**

In Switzerland, people with a severe mental illness and unable to work receive disability benefits (‘IV-pension’). Once they are granted these benefits, the chances to regain competitive employment are usually small. However, previous studies have shown that individual placement and support (IPS) supports a successful reintegration into competitive employment. This study focuses on the integration of newly appointed IV-pensioners, who have received an IV-pension for less than a year.

**Method/design:**

The present pilot project ZHEPP (Zürcher Eingliederungs-Pilot Projekt; engl.: Zurich integration pilot project) is a randomized controlled trial (RCT). The 250 participants will be randomized to either the intervention or the control group. The intervention group receives support of a job coach according to the approach of IPS. Participants in the control group do not receive IPS support. Participation takes a total of two years for each participant. Each group is interviewed every six months (T_0_-T_4_). A two-factor analysis of variance will be conducted with the two factors *group* (intervention versus control group) and *outcome* (employment yes/no). The main criterion of the two-factor analysis will be the number of competitive employment contracts in each group.

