Firstly, IV-pensioners often lack the knowledge of the legal framework and are unsure about their rights. Erroneously, they commonly believe that they are not allowed to apply for a job in the competitive employment market while receiving an IV-pension. The IV-insurance is addressing this issue by providing more information to their pensioners. Secondly, pensioners grow accustomed to not working, thereby increasing the risk of further chronification. To minimize such risks this study includes only new IV-pensioners who have received an IV-pension for less than one year.

During the 1980s the concept of supported employment (SE) was developed in the USA [18] as a reaction to the inefficient *first train*, *then place*-models [19]. SE includes intensive job-search assistance for people with mental illness. Particular attention is given to the clients’ preferences and skills, to assist successful integration into the competitive employment market and to support them while working in competitive employment market [20]. In the USA this approach has been proven to be very successful [21]. However, a transfer of these methods to Europe requires certain structural changes, as Europe differs from the USA concerning job market and welfare system. In 2007 EQOLISE (Enhancing the Quality of Life and Independence of Persons Disabled by Severe Mental Illness through Supported Employment, [19]) was established. In this study, the first of its kind in Europe, participants were trained by job coaches according to the supported employment approach of Individual Placement and Support (IPS) [22]. This study was implemented in six centres across Europe. The results showed that participants assigned to the IPS group were employed more often into competitive employment as compared to the control group. In addition, the IPS participants dropped out of the study less often, and the rates of hospitalization were lower.

Moreover, EQOLISE demonstrated that working in a sheltered work place did not lead to a comparable stabilization of the affected persons [19]. A better state of mental health (e.g. lower anxiety and depression) and a more successful integration into the competitive employment market through the approach of IPS was evident [23].

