### Recruitment and design

Persons who recently received the approval of the IV-pension were invited to an information event. The aim was to inform about the project as well as the supported employment concept IPS. Additionally the job coaches were introduced to the potential participants.

Those interested in participating in our study had the possibility to register and were invited to an one-on-one dialog for further information. Persons who subsequently wished to participate in the study signed the informed consent and were randomized to one of the two groups (control group or the intervention group). During the following two years the participants will be interviewed every six months concerning their well-being, self-esteem, stigma and recovery variables as well as job status (T_0_-T_4_) (List of instruments see Table 1).

**Table 1 T1:** Overview questionnaire based instruments

**Instrument**	**Variable**	**Perspective**	**Measurement point**				
			**T0**	**T1**	**T2**	**T3**	**T4**
Incentive focus scale	Motivation of participant	P	√	√	√	√	√
Client Sociodemographic and Service Receipt Inventory	Sociodemographic facts; medical supply	P/R	√	√	√	√	√
Lacanshire Quality of Life Profile	Quality of Life	P/R	√	√	√	√	√
Symptom checklist 90-revised	Psychological symptoms	P/R	√	√	√	√	√
Rosenberg self esteem scale	Self-esteem	P/R	√	√	√	√	√
Groningen Social Disability Scale	Social role; social disability	P/R	√	√	√	√	√
Global Assessment of Social Disability Scale	Overall psychological disturbance	R	√	√	√	√	√
Internalizes Stigma of Mental Illness Scale	Stigma coping; social drawback	P	√		√		√
Cognitive appraisal	Cognitive appraisal Stigmatization as stressor	P	√		√		√
Perceived Devaluation-Discrimination Questionnaire	Experienced Stigmatization	P	√		√		√
Recovery Assessment Scale	How they feel about themselves and their life	P	√		√		√
Centre für Epidemiological Studies Depression Scale	Depressive symptoms	P	√		√		√
Job discrimination	Experienced discrimination at working place	P	√		√		√
Client Job Status	Working situation	P/JC	√	√	√	√	√
Job Preferences	Job preferences	P/JC	√				
Indiana Job Satisfaction/ Termination Scale	Job satisfaction beginning, while and at the end	P/JC	√	√	√	√	√

*Note*: P: participant, R: Researcher, P/R: Patient by communicating with researcher, P/JC: Patient by communication with job coach; Measurement point: compiled every six month (T0, T1, T2, T3, T4).

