The ZHEPP project is a randomized control trial (RCT) with two factors, *group* (intervention versus control group) and *outcome* (employment yes/no).

The participants of the intervention group are supported by a job coach according to the approach of IPS. Those randomized to the control group are not subject to any intervention by our job coaches, but are merely invited to an interview every six months. The catchment area is the canton of Zurich, Switzerland.

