### Plan of analysis

This study aims to determine, whether job coaching according to IPS enables the successful integration of IV-pensioners into competitive employment.

The total N of this study is 250 participants. Through a Bernoulli randomization the participants are assigned to either the control or the intervention group.

The intervention’s effectiveness is tested by interview based instruments (in total 16 questionnaires). Binary, nominal and interval-scaled data are collected.

A two-factor analysis of variance with the two factors *group* (intervention versus control group) and *outcome* (employment yes/no) will be conducted to control the effectiveness of the intervention. The main criterion of the two-factor analysis will be the quantity of jobs received.

As parameters vary on more than one level a simultaneous comparison in a multilevel model is carried out.

Moreover, the study contains two group comparisons. The persistence of being employed or not in both groups is examined with help of a Cox-regression.

A significance level < 0.05, thus, a confidence interval of 95% is to be achieved.

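### The main criterion is a count of contracts with no per-participant or time-observed basis, so it is open to bias if the two arms are not followed up equally

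*Protocol article*

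**What the plan says.** The abstract (Method/design) fixes the main criterion as a count attached to the arm: "The main criterion of the two-factor analysis will be the number of competitive employment contracts in each group". The Plan of analysis words it differently, but still as a count: "The main criterion of the two-factor analysis will be the quantity of jobs received". Neither sentence says whether the count is per person or per unit of time observed.

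The count is fed by repeated contacts. On follow-up the abstract says "Participation takes a total of two years for each participant", and both groups are seen at five points six months apart. Table 1 lists Client Job Status at every one of those points, with the source code explained in the note as "P/JC: Patient by communication with job coach".

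Three statements bear on whether the arms will be observed equally:

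- The Background reports of the earlier European IPS trial that "the IPS participants dropped out of the study less often".
- Recruitment and design says that controls get no help from the study's job coaches, "but are merely invited to an interview every six months".
- The job-status source code presupposes a job coach, whom only the intervention arm has.

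The Plan of analysis also names a multilevel model, which it does not tie to the job count, and a Cox regression for the persistence of employment status, which is a different question from the main criterion.

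**The concern.** A count of reported contracts grows with the time over which contracts can be reported. If one arm is seen for less time, its count falls even when true job finding is the same. The article describes one arm with continuing coach contact and a possible second route for job information, and another with interview invitations alone. A shortfall in observation would therefore more plausibly fall on the controls.

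At stake is the study's first aim, whether IPS coaching brings more new pensioners into competitive employment. The Discussion says that routine provision of IPS may follow from a positive answer. If the criterion mixes job finding with completeness of follow-up, a positive result cannot be cleanly separated from better retention in the coached arm.

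**Working it through.** The article gives no dropout rate and no expected job rate, so it has no figure of its own to reproduce here. What follows is an illustration.

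**Inputs from the article.** 126 IPS and 124 control participants (Sample size); 24 months of follow-up; contacts at months 0, 6, 12, 18 and 24.

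**Assumptions.** The true job rate p is the same in both arms. Job starts are spread evenly over 24 months. A participant who leaves is equally likely to have the last contact at month 0, 6, 12 or 18, does not return, and has the same job prospects as one who stays. Jobs after the last contact add nothing (the literal count).

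**Step 1: share of follow-up observed.** A leaver is observed on average for (0 + 6 + 12 + 18)/4 = 9 months, and 9/24 = 0.375. With dropout proportion d, the expected recorded rate is p × (1 − d + 0.375d) = p × (1 − 0.625d).

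**Step 2: false-positive rate, one job per person.** With p = 0.30 and dropout of 20% (control) v 10% (IPS):

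- control: 0.30 × (1 − 0.125) = 0.2625
- IPS: 0.30 × (1 − 0.0625) = 0.2813
- standard error: √(0.2813 × 0.7187/126 + 0.2625 × 0.7375/124) = 0.0563
- shift: z = 0.0188/0.0563 = 0.33
- chance of significance favouring IPS: 1 − Φ(1.96 − 0.33) = 5.2%

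The same steps for other assumed values give:

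| True rate, both arms | Dropout, control v IPS | Recorded, control v IPS | Chance of significance for IPS (nominal 2.5%) |
|---|---|---|---|
| 30% | equal | equal | 2.5% |
| 30% | 20% v 10% | 26.3% v 28.1% | 5.2% |
| 30% | 30% v 15% | 24.4% v 27.2% | 7.3% |
| 30% | 40% v 15% | 22.5% v 27.2% | 13.5% |
| 30% | 50% v 20% | 20.6% v 26.3% | 18.2% |
| 40% | 40% v 15% | 30.0% v 36.3% | 18.2% |

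Simulation under the same assumptions at a true 30% gave 5.2% for 20% v 10%, and 13.5% to 13.8% for 40% v 15%.

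**Step 3: the same with a true count.** Let contracts be Poisson with mean 0.4 per person in both arms (assumed). The recorded mean is 0.4 × (1 − 0.625d).

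- 20% v 10%: expected totals 124 × 0.4 × 0.875 = 43.4 and 126 × 0.4 × 0.9375 = 47.2. The ratio per head is 0.9375/0.875 = 1.07, and the false-positive rate for IPS is 5.1%.
- 40% v 15%: totals 124 × 0.4 × 0.75 = 37.2 and 126 × 0.4 × 0.90625 = 45.7. The ratio per head is 1.21, and the false-positive rate is 13.5%.

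Unequal arm sizes alone move a raw total by 126/124 = 1.016, which is minor.

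**Step 4: a different handling of leavers.** Suppose leavers are excluded instead. Keep an overall true rate of 30% in each arm, but assume 15% among leavers and dropout of 40% v 15%. Those who stay then show (0.30 − 0.40 × 0.15)/0.60 = 40.0% in controls and (0.30 − 0.15 × 0.15)/0.85 = 32.6% in IPS. The bias now runs against IPS.

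**The case against.** The strongest reply is that the article nowhere scores leavers as jobless. An analysis of variance needs participant-level values, the stated outcome factor (employment yes/no) is a per-person variable, and the rule for missing interviews may sit in a fuller document that is not shown. All of this is right. A reader might infer that the plan builds in a one-directional bias towards IPS. The text does not support that, because the direction is fixed only under the literal count, and step 4 shows it can reverse.

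A reader might also infer that the authors expect more dropout among controls. They do not say so. The Background reports another trial's result, without a rate and without a forecast for this one.

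The size is equally open. The larger figures need 40% to 50% control dropout and a gap of 25 to 30 points, for which the article gives no basis. People who miss an interview may also return and report past jobs; the discrimination items, for instance, look back a full year.

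Finally, the calculation in step 2 would come out the same for a per-person yes/no outcome if missing were scored as no. That is correct, and it means that a per-participant definition alone is not enough; time observed has to enter as well.

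What survives is the criterion itself. It is stated twice, both times as a count without an observation basis, and no other planned analysis is said to replace it. That is a fault in what the article fixes, not only a missing rule.

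**Conclusion.** The point holds as a weakness in the stated main criterion. A count with no per-participant or time-observed basis, built from six-monthly contacts, is open to bias from unequal follow-up. The article's own account of the earlier trial, of control contact and of the job-status source gives reason to guard against it.

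If unobserved jobs count as none, the bias favours IPS. It is modest at a 10-point dropout gap (about 5% against a nominal 2.5%) and material at a 25-point gap (about 14%), given a 30% job rate, even job timing and leavers no different from stayers. These rates are assumptions, so the figures show how sensitive the criterion is and do not predict what will happen in this trial. The change should be made. Confidence is medium, because the size and, under other handling, the direction cannot be derived from the article.

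**What to change.** Define the main outcome for each randomised participant and account for time observed. Either of these would do:

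- time from randomisation to first competitive job, with everyone randomised included and censored at the last date on which job status is known; or
- the number of competitive jobs per participant, in a count model with log months observed as offset.

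Use the same definition in the abstract and in the Plan of analysis.

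Obtain job start and end dates by the same route in both arms, and state who completes the job-status form for controls. For participants who decline further full interviews, one short question on job dates up to month 24 would recover most of what is lost. It would also reduce reliance on the assumption, shared by both models, that leaving is unrelated to job prospects.

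The cost is a change of analysis wording and one short contact for those who stop attending. The estimated IPS effect may come out smaller, or its interval wider.

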**Discussion:**

This study will focus on the impact of IPS on new IV-pensioners and aims to identify predictors for a successful integration. Furthermore, we will examine the effect of IPS on stigma variables and recovery orientation.

**Trial registration:**

ISRCTN54951166

## Background

In general only 10 to 20% of people who suffer from severe mental illness are employed in the competitive employment market [1]. However, most people suffering from a severe mental illness would actually like to work in the competitive employment market [2]. As persons with mental illness often perceived as unreliable employees by potential employers, the reintegration can be very difficult [3]. Additionally, health professionals frequently discourage patients from applying for competitive employment, because they are convinced that a stressful surrounding will lead to a destabilization of the patient [4,5].

In Switzerland, people suffering from a physical or mental illness which prevents them from working receive a financial support (so called IV-pension) from the social services SVA Zurich (Sozialversicherungsanstalt Zürich, engl.: social benefits centre of Zurich, so called IV-institution). Over the past 12 years the IV-institution has registered a continual increase of people receiving an IV-pension because of mental illness. In the year 2000 around 77 000 people received this contribution in Switzerland but by 2011 the amount of IV-pensioners had increased to 102 000.

Before receiving the IV-pension, the IV-institution offers several possibilities of supporting a reintegration into the competitive employment market (e.g. vocational training, intervention of apprenticeship). However, after receiving the approval for an IV-pension auxiliary measures to support a reintegration are limited. In consequence IV-pensioners may not feel sufficiently supported by the IV-insurance. During our information gatherings many IV-pensioners stated that the only thing they knew about the IV-insurance was that it provided assistance in finding sheltered work.

Most mentally ill people including IV-pensioners state that they are not keen to work in such places and would rather be integrated into competitive employment [4]. They feared that working in a sheltered work place will lead to a high risk of having to stay in this environment [6].

Furthermore, patients state that the integration into the competitive employment market leads to more self-esteem and an increased quality of life [7] due to receiving a salary as well as the chance of finding more social contacts [8]. Mentioning working in a sheltered employment also means revealing one’s illness and hence a fear of not being accepted in society [9].

The stigma associated with psychiatric disorders can have a major negative impact on individuals with mental illness. Stigma comes in two forms [10]. First, members of the general public, for example employers, can endorse negative stereotypes about people with mental illness and discriminate against them, e.g. not inviting persons with mental illness for job interviews. This is referred to as public stigma. Second, self-stigma occurs if people with mental illness agree with those negative stereotypes and turn them against themselves, undermining their self-esteem, self-efficacy and motivation to pursue life goals such as employment [11]. People with mental illness can also suffer from stigma as a stressor if they perceive stigma as a potential harm that exceeds their coping resources [12,13].

There are two main reasons to examine stigma variables in the context of IPS [14]: (i) fear of public stigma as well as self-stigma may stop people from seeking competitive employment, therefore increased levels of stigma variables could predict less positive IPS outcomes; (ii) re-entering the workforce and the associated social roles and contacts might lead to an increased perception of social inclusion among people with mental illness, resulting in less self-stigma, perceived public stigma as well as stigma-related stress; therefore stigma variables can be assessed as secondary outcomes of IPS.

The traditional approach in rehabilitating people with mental illness has been *first train*, *then place*[15]. In this approach possible difficult situations concerning the employment are trained beforehand. After training these situations the person is placed in competitive employment. Practicing the various scenarios which could occur in the future employment is useful, but the situations in real life are generally much tougher than expected and differ from the trained situations. In many cases the job was chosen for the client, and not by the client, and was thus not suited to the client`s needs and preferences [1]. *First train*, *then place* has drawbacks, as people become ill and are not able to hold their jobs for a long time [16]. In consequence many of the people treated by this approach are only able to work in a sheltered workplace [17].

As frontline services to integrate IV-pensioners into the competitive employment market are almost non-existent, two problems emerge.

Firstly, IV-pensioners often lack the knowledge of the legal framework and are unsure about their rights. Erroneously, they commonly believe that they are not allowed to apply for a job in the competitive employment market while receiving an IV-pension. The IV-insurance is addressing this issue by providing more information to their pensioners. Secondly, pensioners grow accustomed to not working, thereby increasing the risk of further chronification. To minimize such risks this study includes only new IV-pensioners who have received an IV-pension for less than one year.

During the 1980s the concept of supported employment (SE) was developed in the USA [18] as a reaction to the inefficient *first train*, *then place*-models [19]. SE includes intensive job-search assistance for people with mental illness. Particular attention is given to the clients’ preferences and skills, to assist successful integration into the competitive employment market and to support them while working in competitive employment market [20]. In the USA this approach has been proven to be very successful [21]. However, a transfer of these methods to Europe requires certain structural changes, as Europe differs from the USA concerning job market and welfare system. In 2007 EQOLISE (Enhancing the Quality of Life and Independence of Persons Disabled by Severe Mental Illness through Supported Employment, [19]) was established. In this study, the first of its kind in Europe, participants were trained by job coaches according to the supported employment approach of Individual Placement and Support (IPS) [22]. This study was implemented in six centres across Europe. The results showed that participants assigned to the IPS group were employed more often into competitive employment as compared to the control group. In addition, the IPS participants dropped out of the study less often, and the rates of hospitalization were lower.

Moreover, EQOLISE demonstrated that working in a sheltered work place did not lead to a comparable stabilization of the affected persons [19]. A better state of mental health (e.g. lower anxiety and depression) and a more successful integration into the competitive employment market through the approach of IPS was evident [23].

The supported employment concept IPS, which was used in the EQOLISE study as well as in the study presented here, ensures the immediate support of a job coach and the direct integration into competitive employment. Job coaches support the client by searching for vacant jobs, assisting applications, as well as coaching the client in working situations [24]. If the client and employer approve, job coaches may also support the employer and the workmates.

